## Abstract

**Background:**

The World Health Organization has prioritized the use of new technologies to assist in health care delivery in resource-limited settings. Findings suggest that the use of SMS on mobile phones is an advantageous application in health care delivery, especially in communities with an increasing use of this device.

**Objective:**

The main aim of this trial is to assess whether sending weekly motivational text messages (SMS) through mobile phones versus no text messaging will improve retention in care and promote adherence to treatment and health outcomes among patients receiving HIV treatment in Fako Division of Cameroon.

**Methods:**

This is a multisite randomized controlled single-blinded trial. Computer-generated random block sizes shall be used to produce a randomization list. Participants shall be randomly allocated into the intervention and control groups determined by serially numbered sealed opaque envelopes. The 156 participants will either receive the mobile phone text message or usual standard of care. We hypothesize that sending weekly motivational SMS reminders will produce a change in behavior to enhance retention; treatment adherence; and, hence, health outcomes. Participants shall be evaluated and data collected at baseline and then at 2, 4, and 6 months after the launch of the intervention. Text messages shall be sent out, and the delivery will be recorded. Primary outcome measures are retention in care and adherence to treatment. Secondary outcomes are clinical (weight, body mass index), biological (virologic suppression, tuberculosis coinfection), quality of life, treatment discontinuation, and mortality. The analysis shall be by intention-to-treat. Analysis of covariates shall be performed to determine factors influencing outcomes.

**Results:**

Recruitment and random allocation are complete; 160 participants were allocated into 3 groups (52 in the single SMS, 55 in the double SMS, and 53 in the control). Data collection and analysis are ongoing, and statistical results will be available by the end of August 2019.

**Conclusions:**

The interventions will contribute to an improved understanding of which intervention types can be feasible in improving retention in care and promoting adherence to antiretroviral therapy.

**Trial Registration:**

Pan African Clinical Trial Registry in South Africa PACTR201802003035922; https://pactr.samrc.ac.za/TrialDisplay.aspx?TrialID=3035

**International Registered Report Identifier (IRRID):**

DERR1-10.2196/15680

## Introduction

In patients infected with HIV, viral replication can be effectively suppressed with antiretroviral therapy (ART), allowing the body’s immune system to restore and function adequately [1]. Suppressed viral replication in HIV infection has been proven to dramatically reduce mortality and morbidity rates, leading to improved quality of life and improved perceptions on HIV/AIDS from a death sentence to a manageable chronic disease [2]. Yet, the population effect of ART depends on high coverage and sustained adherence to treatment among people living with HIV [3].

The SMS of the mobile phone is an inexpensive and suitable means of communication that can be used in conveying health messages to persons who own or have access to mobile phones. In 2013, 97% of the world’s population were mobile phone subscribers [4]. Moreover, by 2015, 71 per 100 inhabitants of Cameroon were accessing mobile phones [5].

Study protocols on the use of SMS technology to promote adherence to ART have been developed in Kenya [6], India [7], and Cameroon [8]. In 2005, the World Health Organization spelled out the use of new technologies to assist health care delivery in resource-limited settings [9]. Since then, the SMS has shown promising results in improving HIV health care delivery and communication between health personnel and clients, and as an appointment reminder in trials conducted in Kenya [10], Cameroon [11,12], South Africa [13], and elsewhere [14].

The use of text messages in improving adherence to primary care has been found to be more profitable than phone calls [15]. Patient-centered mobile health (mHealth) interventions have had promising outcomes in sickle cell disease management [16]. Systematic reviews have pointed to the success of mobile phone text messaging interventions in improving medication adherence among people living with chronic diseases [17-19]. These findings suggest the use of SMS as a more advantageous application of the mobile phone in health care delivery especially in communities with increasing use of these devices.

Only a single mHealth intervention has been conducted in Cameroon and included only one hospital and 198 participants for a period of 6 months [11]. This lone Cameroonian mHealth intervention together with those conducted elsewhere [10,13,15] has shown promising results on ART adherence and retention in HIV care. Thus, further research involving patients from different treatment centers, and most especially in the phase of government efforts to fight HIV/AIDS, is warranted in Cameroon. This study is timely as it is based on this strategy to improve and promote ART adherence and retention in care in Cameroon. Furthermore, the study will enhance our understanding of the extent that mHealth intervention promotes healthy behaviors and supports psychosocial well-being among patients receiving treatment for chronic diseases. Therefore, this study will contribute to an improved understanding of which text message frequency can be feasible when, why, and for whom.

The goal of this trial is to determine whether sending weekly motivational text messages through mobile phones versus no text messaging will improve retention in care and promote adherence to treatments and health outcomes among patients receiving HIV treatments over a 6-month period. We hypothesize that sending weekly motivational text message reminders will produce a change in behavior to enhance retention; treatment adherence; and, hence, health outcomes.

Participants will be recruited from two hospitals approved to provide free HIV treatment services in Fako Division of the South West Region of Cameroon.

## Methods

The trial was registered with the Pan African Clinical Trial Registry [20] in South Africa on February 1, 2018. The unique identification number for the protocol is PACTR201802003035922.

### Study Design

The design rests on a three-arm, randomized controlled trial with two intervention arms and one control group. The trial shall be single-blinded where the investigators and participants shall not be blinded to the intervention, whereas interviewers and data analysts will be blinded to group allocation. The intervention shall include the use of mobile cellphone SMS in addition to the standard of care provided to the clients. Participants shall be randomly allocated in a 1:1:1 ratio to one of three arms prior to the beginning of the intervention: (1) once weekly mobile phone SMS, (2) twice weekly mobile phone SMS, and (3) a control group that shall not receive mobile cellphone SMS. Clients will be recruited from the government-approved centers of the Regional Hospital Buea and Regional Hospital Limbe providing HIV treatment services.

### Randomization

This is a parallel-group design evaluating the effects of adding once-weekly mobile phone text messages and twice-weekly mobile phone text messages to the usual standard of care (intervention) versus usual standard of care alone (control) among HIV clients receiving ART. Eligible and consenting participants shall be randomized to interventions and control arms using a 1:1:1 allocation ratio by the opaque sealed envelope method. A computer-generated randomization list will be produced using random block sizes of 2, 4, and 6 by the research biostatistician. The allocation codes shall then be put in serially numbered opaque sealed envelopes and administered by the research staff at the various hospitals. Trained interviewers, who shall be blinded to group allocation, will collect data using pretested questionnaires containing sociodemographic data, clinical information, retention, and adherence measures at baseline and at 2, 4, and 6 months. The biostatistician shall also be blinded to group allocation. Blood samples will be collected and analyzed for viral load during the trial once a participant has been on ART for at least 6 months. The time schedule of enrollment, interventions, and assessments are summarized in Figure 1.

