### Analysis Plan

The CONSORT (Consolidated Standards of Reporting Trials) guidelines will be used in reporting the results. The biostatistician shall be blinded to the group allocation. The process of client selection and flow throughout the study will be summarized using a flow diagram. The analysis of client demographics and outcome variables shall be summarized using descriptive summary measures, expressed as mean (standard deviation) or median (range) for continuous variables and number (percentages) for categorical variables. All outcomes shall be analyzed using an intention-to-treat principle where data from participants shall be analyzed according to the group to which they were randomized even if they do not receive the allocated intervention. Missing data shall be handled using the multiple-imputation method. The student *t* test and analysis of variance for comparing group means will be used. All statistical tests shall be performed using two-sided tests at the 5% level of significance. The Bonferroni method shall be used to adjust the level of significance for testing of secondary outcomes to keep the overall level at an alpha of 5%. For all group comparisons, the results shall be expressed as an effect (or risk ratio for binary outcomes), corresponding two-sided 95% confidence intervals, and associated *P* values. *P* values shall be reported to three decimal places with values less than .001 reported as <.001. Adjusted analyses using baseline variables shall be performed using regression techniques to determine the continuing influence of key baseline characteristics on the outcomes. The Kaplan-Meier survival analysis will be used for timed variables like mortality. All analyses will be performed using SPSS version 25.0 (IBM Corp) for Windows. Adherence will be measured both as a continuous outcome (change in adherence) and as a binary outcome (ie, adherent, 95% of pills taken, or nonadherent, <95% of pills taken) following the composite adherence score method. Adherence data shall be handled in a number of ways, reported as the number of doses respected, and shall be combined into a composite score. The effects of the intervention shall be reported on all the measures of adherence used and will be compared for discrepancies.

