## Results

Recruitment of participants in the trial took place in May and June 2018. Recruited participates were randomly allocated to the intervention and control arms at the start of the intervention in July 2018.

A total of 160 participants have been recruited and randomly allocated into the intervention and control groups. Participants were allocated into 3 groups (52 in the once weekly SMS, 55 in the twice weekly SMS, and 53 in the control). Data collection and analysis are ongoing, and statistical results will be available by the end of August 2019.

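### The biostatistician who produces the randomization list is also declared blinded to allocation, so the procedure as described does not achieve the analyst blinding the plan claims

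*Protocol article*

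**What the plan says.** Four places in the protocol article bear on this point.

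- **Randomization**, on who makes the list: "A computer-generated randomization list will be produced using random block sizes of 2, 4, and 6 by the research biostatistician".
- **Randomization**, later in the same paragraph: "The biostatistician shall also be blinded to group allocation".
- **Analysis Plan**, near its start: "The biostatistician shall be blinded to the group allocation". This ties the biostatistician to the analysis.
- **Study Design**, on who is masked: "interviewers and data analysts will be blinded to group allocation". The same sentence leaves investigators and participants unmasked.

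On what happens to the list, Randomization adds: "The allocation codes shall then be put in serially numbered opaque sealed envelopes and administered by the research staff at the various hospitals". It does not say that the codes are neutral, or that someone other than the biostatistician holds their meaning.

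The Results section gives the arm sizes by name, "52 in the once weekly SMS, 55 in the twice weekly SMS, and 53 in the control", and the status at that time: "Data collection and analysis are ongoing, and statistical results will be available by the end of August 2019". The Abstract gives the same sizes.

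**The concern.** Whoever generates an allocation list knows it unless a specific step hides it from them. The article describes no such step and then calls the same role blinded. A reader who relies on the blinding statement to judge risk of bias would credit the trial with a protection that its procedure does not supply.

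Participants and investigators know the allocation, so masking rests on two groups: the interviewers who collect the data and the analysts. This point concerns the second.

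Analyst masking has some work to do here because the adherence analysis leaves choices open. Study Objectives sets out four measures and a composite. Sample Size Determination takes the visual analog scale as the primary measure of effect. The Analysis Plan treats adherence in both binary and continuous form and leaves the handling of the adherence data loosely described. An analyst who knows the arms could settle these choices with the direction of the effect in view.

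**Working it through.** **Step 1: the roles side by side.**

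| Place in the protocol article | Role named | What is said of it |
|---|---|---|
| Randomization | research biostatistician | produces the list |
| Randomization | biostatistician | blinded to allocation |
| Analysis Plan | biostatistician | blinded to allocation |
| Study Design | data analysts | blinded to allocation |

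The first two rows come from one paragraph, which mentions only one biostatistician. Read plainly, they describe the same person, and the two statements conflict unless the list was masked from its author. No masking is stated.

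**Step 2: would coded arms repair this?** Suppose the analysis file carried the letters A, B and C in place of arm names.

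- Inputs, from Results: once weekly 52, twice weekly 55, control 53.
- Check against the stated total: 52 + 55 + 53 = 160, which agrees.
- Possible labelings of three coded arms: 3! = 6.
- Labelings that fit three different published counts: 1.
- For comparison, two equal arms would leave 2 fitting labelings, and three equal arms would leave all 6.

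The unequal sizes therefore identify every arm for someone who knows the published counts and can tabulate all 160 participants by code. The Analysis Plan's intention-to-treat principle and multiple imputation make such a full file likely, because randomized participants stay in their arms.

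**Step 3: where that identification fails.** It depends on a complete file. Sample Size Determination allows for 10% dropout, and retention is itself an outcome, so a file of attended visits will be short. The once-weekly and control arms differ by one participant. Five losses in one and six in the other would give 52 − 5 = 47 and 53 − 6 = 47, and counting rows would no longer separate them.

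**Step 4: effect on other figures.** None. Sample size, power, alpha and the interviewer-blinding statement do not depend on who analyses the data.

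**The case against.** The strongest reply is that this is a condensed article. Study Design speaks of data analysts in the plural, so the person who made the list need not be the only analyst. The envelopes hold allocation codes, and the full protocol or analysis plan may say who holds the key. It is fair that an article may leave such detail out. But the article does not merely stay silent: it gives one role the list and declares that role blinded, and the Analysis Plan places that role in the analysis. The contradiction needs resolving whatever other documents contain.

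A reader might go further and infer three things that the documents do not support.

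- *That analyst blinding does not exist and no coding could restore it.* The text shows only that the described procedure does not achieve it. A separate analyst who had not seen the counts, or who worked on scrambled allocations, could still be masked.
- *That coded arms are certain to be identified.* This holds only under the conditions in Step 2. The arm sizes are an outcome of recruitment, and the plan was for 52 per arm. They are not in themselves a planning error.
- *That a large number of adherence results is open to free selection.* Multiplying measures, forms, visits and contrasts overstates the choice. Table 1 fixes each of the four component measures as binary with a 95% cut, and the binary-and-continuous sentence in the Analysis Plan is most naturally read as applying to the composite. The Analysis Plan also undertakes to report the effect on every adherence measure and to compare them for discrepancies. That limits selective choice among measures, though it does not settle which result leads.

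It is also fair that analyst blinding is not the only safeguard. The interviewers, who collect the retention and adherence data, are separately stated to be blinded.

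**Conclusion.** The concern holds in a limited form. The plan claims analyst blinding, and its own description of who makes the list does not deliver it. This rests on reading the research biostatistician and the biostatistician as one role, which is the natural reading when no other is mentioned, and on the absence of any stated masking or independent key.

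The weakness of simple arm codes is a supporting point. It assumes an analyst who knows the published sizes and sees all 160 participants by code; then only 1 of 6 labelings fits.

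No calculated figure changes, and the size of any bias cannot be estimated from the document. What changes is what a reader may conclude about one of the trial's two masking safeguards. The correction should be made, but the point does not undermine the design.

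**What to change.** 1. Write and lock the outcome analysis programs on a dataset in which arm labels have been randomly shuffled across participants, then run them once on the true allocation. Shuffling keeps the arm sizes but breaks the link between arm and outcome, so recognising an arm by its size reveals nothing about the effect. Replacing arm names by letters would not do this.
2. Give this work to an existing team member who neither made nor held the list, if one is available, and say so in Randomization and the Analysis Plan.
3. If this is not done, or the analysis already under way is too far advanced, withdraw the blinded-biostatistician statements in Randomization and the Analysis Plan and the data-analyst part of the blinding sentence in Study Design, and report the analyst as unblinded. The interviewer-blinding statement can stay.

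Cost: a few hours to prepare the shuffled dataset, plus wording. A separate analyst may need extra staff time. The third option costs only a less favourable blinding statement and remains available at any stage.

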**Figure 1 figure1:**
[figure not shown]
Recruitment and random allocation into the text messaging and control groups. AFB: acid-fast bacilli; ART: antiretroviral therapy; TB: tuberculosis; WHO: World Health Organization.

### Trial Setting

Cameroon is a sub-Saharan central African country made of ten regions and a population of over 24 million inhabitants [21]. The study will be implemented in Fako Division of the South West Region of Cameroon. The adult prevalence of HIV in the country was 3.4% in 2018 [22]. The adult prevalence of HIV in the South West Region was 3.6% in 2018 [22]. Most inhabitants practice agriculture as the main economic activity. The region has two seasons: the dry season from October to March and the wet season from April to September. Almost all ethnic groups in Cameroon are represented in the region, attracted by the fertile volcanic soil and the Cameroon Development Corporation, a giant agricultural corporation that seconds the state of Cameroon in employment. The two hospitals selected for the trial have government-approved centers offering free treatment and care services for HIV to the population of the region. Participants will be residents in their various communities and support groups while visiting these treatment hospitals for routine care during the entire study period. As per the Cameroonian Ministry of Public Health national guidelines, newly diagnosed clients are initiated on free nonnucleotide reverse transcriptase inhibitors–based ART irrespective of their viral load count or CD_4_^+^ T cell count [11]. Recently, HIV clients initiating ART were systematically placed on isoniazid prophylaxis for the first 6 months of their ART. These are the largest treatment centers in the region and offer enormous potential for recruitment.

### Participants: Inclusion and Exclusion Criteria

The study population shall include HIV clients either coinfected with or without tuberculosis who come to the hospital for a routine health evaluation. Participants shall be consecutively recruited and randomly allocated to the intervention and control groups.

We shall include clients who are 21 years or older, have access to or own a mobile phone and can read text messages, and who have been on ART for at least a month and planned to live in Cameroon during the period of the study. We shall place more emphasis on clients who have started ART for at least 1 month to measure the differential effects for clients initiating ART versus those who have been under treatment for longer durations. Informed consent is a prerequisite for participating in the study and shall be provided orally and in writing.

We shall exclude clients who have been on ART for less than a month and who are younger than 21 years. Clients who have used ART for at least 1 month are chosen to enable us to be able to calculate a baseline figure for treatment adherence.

### Intervention

The HIV clients will be receiving ART for free from the hospital staff at the HIV treatment centers. The HIV clients who shall be coinfected with tuberculosis shall also receive directly observed treatment short-course for free. This is the usual standard of care for people living with HIV/AIDS and tuberculosis in Cameroon [23]. Patients with HIV on any of these treatments shall be randomized to receive mobile phone text message reminders. The trial shall comprise 2 intervention groups and 1 control group to investigate the impact of text message reminders on retention in care and adherence to treatment and health outcomes.

**Sample SMS to improve retention in care**
You are so loved. Handle your health with care, visit us on xx-xx-xxxx.You are very important. Do not forget your visit on xx-xx-xxxx.Are you busy? This is why I remind you to come for your visit on xx-xx-xxxx.Your health is important. Come for your appointment on xx-xx-xxxx.
**Sample SMS to promote adherence to treatment**
Your health is important. Take your food.You are very important. Do not play with your health. Take your food.You are so loved. Handle your health with great care. Take your food.Are you very busy? This is why I remind you to regularly take your food.

### Control

The routine practice in Cameroon is that, at ART initiation, the responsibilities of the treatment centers usually explain the side effects of medications and problems associated with poor adherence to the clients prior to dispensing drugs. All participants including those in the control arm have received this educational message during their routine hospital visits. Participants randomly allocated to the control group shall not receive mobile phone SMS. However, they shall receive ART, be screened for tuberculosis coinfection, and be interviewed alongside the other participants.

